#### 4 TRIAL DESIGN

This study is an exploratory, dose-escalating pilot trial to test the feasibility, safety and preliminary efficacy of aerosolized lung delivery of surfactant, a medicine with a known safety profile, to improve the oxygenation and pulmonary compliance of adult patients diagnosed with moderate to severe COVID-19 associated lung injury with increasing oxygenation requirements.

The timing of escalating dosing and assessment of clinical response is based on the rapid oxygenation response of infants with surfactant deficiency ([Collaborative European Multicenter Study Group 1988](#)) and the clinical response described in adults after endobronchial administration of surfactant in ARDS ([Walmrath 2002](#)). Nevertheless, it is acknowledged that the optimal dose required for surfactant replacement therapy in adults and the rate of clinical response in patients with COVID-19 are unknown. Therefore, we propose a dose-escalating, adaptive trial design in which the feasibility of administration of aerosolized surfactant and the clinical response in mechanically ventilated COVID-19 patients are assessed. The dosing regimen may be adjusted based on accumulating data and may depend on the dose required to achieve a clinical response and the speed with which that response is seen.

Patients will enter the study and will be randomised to 3:2 for the treatment and control arms where they will receive three doses of Alveofact® via nebulizer or the control arm where treatment will follow standard of care.

Patients in the treatment arm will be assigned into cohorts sequentially as follows:

- **COHORT 1:** 3 patients will receive 10 vials (1080 mg) each of Alveofact® at dosing times of 0 hours, 8 hours and 24 hours. 2 controls.

- **COHORT 2:** 3 patients will receive 10 vials (1080 mg) of Alveofact® at dosing times of 0 hours and 8 hours, and 30 vials (3240 mg) of Alveofact® at a dosing time of 24 hours. 2 controls
- **COHORT 3:** 3 patients will receive 10 vials (1080 mg) of Alveofact® at a dosing time of 0 hours, and 30 vials (3240 mg) of Alveofact® at dosing times of 8 hours and 24 hours. 2 controls
- **COHORT 4:** 3 patients will receive 30 (3240 mg) vials each of Alveofact® at dosing times of 0 hours, 8 hours and 24 hours. 2 controls

Control arm:

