**CONTROL:** Each cohort of 3 patients (in the treatment arm) will have 2 patients acting as controls (5 patients per cohort; total control n=8). The protocol for the control arm will be identical to the treatment arm except for surfactant nebulization.

After each cohort has completed treatment (or equivalent time for controls), the investigators will pause to review the outcomes of the treatment based on the co-primary outcomes (PaO2/FiO2 ratio and Ventilation index at 48 hours), reported adverse events and any additional safety or feasibility considerations. Additional trial outcome data may be taken into account if considered important in the opinion of the principal and chief investigators or if requested by the DSMB or TSC.

The decision to progress may be: 1. increase dose to next cohort level according to planned schedule (see below); 2. decrease dose to previous cohort level according to planned schedule (see below); 3. decrease dose to alternative level (specifically for cohort 1); 4. maintain dosage at current level. If there is a substantial and sustained improvement in the outcomes of a cohort, the subsequent cohorts may continue with the same dose as the previous cohort. If no improvement is observed, the subsequent cohort may increase the dosage. Early and substantial improvement during administration of the drug, or adverse events thought to be a safety concern, may prompt the investigators to reduce the administered dose during the conduct of the study.

Decisions relating to trial progression and dose escalation/maintenance/reduction will be made by the TSC after review of data by the DSMB. The DSMB will meet immediately prior to the TSC in open session but may meet in closed session at the request of any members of the DSMB or TSC. The TSC will meet after the DSMB and receive a verbal update from the DSMB. The TSC will be the final arbiter of trial progression and dose escalation/maintenance/reduction decisions. The majority of the TSC and all members of the DSMB will be independent of the trial investigators and trial conduct. An extraordinary meeting of the DSMB may be convened if the investigators have any safety concerns. Such a meeting would make recommendations to the TSC on trial continuation/discontinuation. The trial will not be discontinued on the basis of lack of efficacy. The trial may be stopped early on the basis of safety or feasibility concerns.

[figure not shown]

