## 8.7 Dosage modifications

In an event when the administration of 30 vials is not practical, doses may drop to 20 or 10 vials, depending on feasibility. In the event clear efficacy is observed in cohort 1, doses may drop below 10 vials or dosing times may be reduced.

Progression and dosing modifications of subsequent cohorts will be decided by teleconference of the trial steering committee. Any safety concerns would be referred to the independent DSMB on completion of dosing of each cohort of 3 patients + 24 hours to enable collection of physiological outcomes.

The DSMB will actively monitor emerging safety and efficacy data to make recommendations about early study closure or the initiation of a larger randomised controlled clinical trial.

The dose administered cannot be modified due to patient / personal legal representative request.

Given the severity of the illness in ventilated Covid-19 patients, safety data will be interpreted with caution and will not be formally compared between active intervention and control groups.

- Dosing will be stopped in individual patients upon persistent deterioration of oxygenation during or after surfactant administration
- Study stopping rules for futility or efficacy are provided in the statistical analysis section.
- The protocol team will review emerging AE/SAE/SADEs data daily. If 3 or more patients develop the same SAE after administration of study drug, the study will be paused pending review by the DSMB. The study may also pause at the discretion of the Principal Investigator if there are a significant number of unexpected AEs/SAEs/SADEs and referred to the DSMB for review.
- The DSMB will formally review the safety data after every three subjects and is available for ad hoc reviews for other safety concerns as noted above.

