### Efficacy

The goal of this study is to assess the preliminary efficacy and safety of surfactant administration, identify an efficacy signal quickly (if present) to consider initiation of a larger randomised controlled clinical trial, and assess the potential impact of total dose on preliminary efficacy.

The change in PaO2/FiO2 ratio relative to baseline at 24 hours after the last dose of surfactant and the change in Ventilation Index relative to baseline at 24 hours after the last dose of surfactant will be analysed separately. For each endpoint, a test for a total dose-response effect using a model-based multiple contrast test (Bretz et al, 2005) will be performed. Candidate dose-response models will include linear and Emax. The change in PaO2/FiO2 and change in Ventilation Index may be transformed for analysis (e.g., log transformed) to better satisfy normality assumptions of model residuals. The primary analysis will be done on patients with observed data at 24 hours ("completers"), though sensitivity analyses will also be performed if data are missing at 24 hours in an informative manner (e.g., due to death) where a non-parametric approach can accommodate missing data by assigning the worst rank.

The table below shows the power to show a significant dose response under varying assumed true dose response curves when using 12 matched controls.

| CV                                      | Relative change from baseline, on average |                           |                           |                           |                           | Power to show dose response |
|-----------------------------------------|-------------------------------------------|---------------------------|---------------------------|---------------------------|---------------------------|-----------------------------|
|                                         | Control                                   | Cohort 1 (30 total vials) | Cohort 2 (50 total vials) | Cohort 3 (70 total vials) | Cohort 4 (90 total vials) |                             |
| 20%                                     | 0%                                        | 0%                        | 0%                        | 0%                        | 0%                        | 0.05                        |

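### The power table assumes every cohort escalates to plan; if the hold option in section 4 is used, power for a rising dose response is lower, by an amount the protocol does not fix

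*Protocol*

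**What the plan says.** **Test and table (section 10, Efficacy).** The final efficacy analysis is "a test for a total dose-response effect using a model-based multiple contrast test", run separately for each co-primary endpoint. "Candidate dose-response models will include linear and Emax". The table is introduced with the words "The table below shows the power to show a significant dose response under varying assumed true dose response curves", "when using 12 matched controls", and its columns equate cohorts 1 to 4 with 30, 50, 70 and 90 total vials. For the rising curve it prints 0.89 at CV 20% and 0.77 at CV 25%. The text below the table calls power reasonable at CV 20% when the true increase is at least 20-30% in two or more cohorts. It attaches no condition about the dose path.

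**Design (section 4).** "we propose a dose-escalating, adaptive trial design". After each cohort the dose may go up, go down or stay, on review of the same two outcomes that the dose-response test analyses. After a substantial and sustained improvement, "the subsequent cohorts may continue with the same dose as the previous cohort". The trial steering committee decides, after review by the safety board. Section 4 plans 2 controls per cohort, 8 in all.

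**Dose changes (section 8.7, Dosage modifications).** If 30 vials prove impractical, "doses may drop to 20 or 10 vials, depending on feasibility".

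**The concern.** The test draws its leverage from the spread of total doses. The high-power row of the table needs escalation to continue past cohorts whose true improvements are 20% and 30%. Section 10 itself gives a change of at least 20% as an example of a high one when it discusses interim efficacy. So in the scenario where the drug works increasingly well with dose, section 4 may favour holding, while the table assumes that no hold occurs.

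The protocol says that significant dose-response fits may inform doses for later studies. If cohorts are held and the test is then not significant, a reader would judge that result against 0.89, which belongs to a path the trial did not follow.

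**Working it through.** **Inputs from the protocol.** 3 treated patients per cohort; total doses 30/50/70/90 vials; 12 controls in the table and 4 × 2 = 8 in section 4; CV 20% or 25%; linear and Emax candidate models; rejection rate 0.05 in the null row.

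**Inputs assumed.** Log-scale analysis, which the protocol permits; one-sided 5% test; Emax ED50 between 10 and 45 vials, where the choice makes little difference; pooled variance. The log SD is √ln(1 + CV²), which is √ln(1.04) = 0.198 at CV 20%.

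**Step 1: reproduce the table.** With 3 patients at each of the four doses and 12 controls, the rising curve at CV 20% gives 0.90 against the printed 0.89. All 12 rows agree within about 2 points. At 2,000 simulations, the simulation error of the printed value is √(0.89 × 0.11 / 2000) = 0.007. The table therefore describes full escalation. Alternatives fit worse: two-sided 0.82-0.83, raw scale 0.96, 8 controls 0.84-0.85.

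**Step 2: fix the dose path, with no threshold assumed.** Rising curve, CV 20%, 12 controls:

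| Path | Power |
|---|---|
| Full escalation | 0.90 |
| Held at 70 from cohort 3 | 0.84 |
| Held at 50 from cohort 2 | 0.64 |
| Held at 30 throughout | 0.31 |

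Section 4 permits each of these paths, so the direction of the effect needs no assumed rule.

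**Step 3: assume a hold rule.** The dose is held permanently once one endpoint's cohort mean change reaches a threshold, and the contrasts are rebuilt for the doses actually given. Rising curve, CV 20%:

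| Hold threshold | 12 controls | 8 controls |
|---|---|---|
| Never held | 0.90 | 0.85 |
| 40% | 0.88 | 0.82 |
| 30% | 0.83 | 0.76 |
| 20% | 0.71 | 0.64 |

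A hand check for the 20% threshold: the standard error of a cohort mean is 0.198/√3 = 0.114.
- Cohort 1 (true 10%) triggers with probability P(Z > (ln 1.2 − ln 1.1)/0.114) = P(Z > 0.76) = 0.22.
- Cohort 2 (true 20%) triggers with probability 0.50.
- Cohort 3 (true 30%) triggers with probability P(Z > (ln 1.2 − ln 1.3)/0.114) = P(Z > −0.70) = 0.76.

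The chance of reaching 90 vials is 0.78 × 0.50 × 0.24 = 0.09, which matches the simulated 9%.

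At CV 25% the 20% threshold takes power from 0.77 to about 0.55 with 12 controls, and from 0.69 to 0.48 with 8.

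**Step 4: other readings.** If the >80% posterior criterion of section 10 is borrowed as a hold rule on one endpoint, power is 0.84-0.86 with 12 controls. If either of two endpoints, taken as independent, can trigger a permanent hold, power runs from 0.56 (20% threshold) to 0.83 (40%).

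**Step 5: what does not get worse.** For the flat 25% row with 12 controls, power is 0.82 with full escalation and 0.86 with the 20% hold. The null rejection rate is 0.051 without a hold and 0.054 with it.

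**The case against.** No printed figure is wrong for the path it describes, and the column labels show that path. Full escalation is the planned schedule in section 4 and in section 8.7 (Dosage schedules). Holding is optional, undefined in number and left to committee judgement, which also weighs safety and feasibility. If the committee escalates throughout, 0.89 stands for 12 controls. The trial is an exploratory pilot of up to 20 patients, and the protocol does not say that its size was derived from this table. A hold would follow apparent benefit, where the separate Bayesian interim look serves the aim of finding a signal early. All of this stands, and it limits the point to how the power is stated.

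A reader might go further and infer that a range such as 69-87% is the trial's power under its own adaptive design. The documents do not support that. They set no threshold, and the only numeric interim criterion serves further trial planning, not dose assignment. Other readings of the same text give anything from 0.31 to 0.90. Nor can one infer a general loss, since flat curves gain. For the highest-cohort-only curve, a simulated loss under lenient rules comes from chance holds in cohorts with no true effect, which the word sustained in section 4 argues against; under the posterior rule that row barely moves (0.65 to 0.63).

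The objection does not remove the unqualified conclusion beneath the table. It is stated for a design that the protocol itself calls adaptive.

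**Conclusion.** The point holds as a matter of conditioning, not of arithmetic. The table gives power for full escalation with 12 controls, and the text presents it without that condition. If holds occur, power for a rising curve at CV 20% is lower. Under the illustrative permanent one-endpoint rules the loss from 0.90 ranges from about 2 points (40% threshold) to about 19 points (20% threshold) with 12 controls. From 0.85 with the planned 8 controls it ranges from about 3 to about 21 points. The control count alone accounts for the step from about 0.90 to 0.85 and is a separate discrepancy. These sizes rest on the assumed hold rules, log-scale analysis and a one-sided 5% test. The validity of the test is not in question.

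**What to change.** 1. Label the table, and the sentence that calls power reasonable, as conditional on every cohort escalating as planned to 30, 50, 70 and 90 total vials.
2. Re-run the table with the planned number of controls, or reconcile the 12 with the 8 of section 4.
3. Add power for the same curves under one lenient and one strict illustrative hold assumption, for example cohort mean changes of 20% and 40%, with contrasts rebuilt for the doses given. Mark these as sensitivity scenarios, not as the trial's power and not as a progression rule.

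The cost is one progression step in the existing simulation, extra columns and a few words. The downside is lower stated power for rising curves. Doses, progression options and the committee's discretion stay as they are.

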| Trial Participants                 | Hospitalised adult patients aged $\geq 18$ years, COVID-19 positive by PCR confirmation, and endotracheally intubated.                                                                                                                                                                                                                |                                                                                                                                                                                                                                                                                                       |
| Planned Sample Size                | Up to 20 hospitalised adult patients ( $\geq 18$ years old)                                                                                                                                                                                                                                                                           |                                                                                                                                                                                                                                                                                                       |
| Treatment duration                 | 24 hours                                                                                                                                                                                                                                                                                                                              |                                                                                                                                                                                                                                                                                                       |

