### 7.3 The randomisation scheme

Patients will be randomised to 3:2 for the treatment and control arms using ALEA Randomisation. ALEA Randomisation is an internet-based service provided by FormsVision BV that supports online patient registration and randomisation and is fully integrated with ALEA eCRF. ALEA Randomisation has been built as a series of components, in order to support interoperability and customised extensions. The components make use of a common standard representation of data and metadata: The Operational Data Model of CDISC. Within ALEA Randomisation, the components share a database for storing and retrieving information about the trial, and a separate database for storing and retrieving patient data. ALEA Randomisation supports the following methods of randomisation for healthcare trials. It supports trials with any number of treatment groups, and randomisation ratios other than 1:1. In this study we will be using the block randomisation schema.

The following series of numbers will comprise the subject identifier:

- Three alpha characters – site code – UHS and UCH
- 2-digit subject number (e.g. 03)

Will be allocated by the site, reflecting the order of consent to the study within the site. For example, the third subject who signed an informed consent form at study UHS will be identified as Subject UHS-03.

The enrolment number will be added to the consent form at the site.

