|                                         | 0%                                        | 0%                        | 0%                        | 0%                        | 50%                       | 0.49                        |
| Based on 2000 simulations for each row. |                                           |                           |                           |                           |                           |                             |

When the true residual CV is 20%, there is reasonable power to detect a dose response for either endpoint when the true increase is at least 20-30% in two or more cohorts. There is limited power to detect a dose response when the effect is only in the highest cohort. Also, when the true residual CV is larger, the power reduces substantially. To reduce residual variability, the fitted model will also adjust for the baseline  $\text{PaO}_2/\text{FiO}_2$  ratio or Ventilation Index as a proxy measure of baseline severity. Significant dose response model fits can be utilized to estimate doses that provide clinically meaningful results and aid in planning for future studies.

Efficacy data will be continuously reviewed after each cohort to assess whether results are compelling enough to suggest initiation of a larger randomised controlled clinical trial. Interim efficacy data will be analysed using a simple Bayesian adaptive approach. After each cohort completes dosing plus 24 hours of follow-up, the posterior distributions of the mean change in  $\text{PaO}_2/\text{FiO}_2$  ratio and the mean change in Ventilation Index will be determined under an assumed normal distribution with a non-informative prior. The change in  $\text{PaO}_2/\text{FiO}_2$  and change in Ventilation Index and may be transformed for analysis (e.g., log transformed) to better satisfy normality assumptions. Interim efficacy will be declared for the purposes of further trial planning if there is relatively high posterior probability (e.g., > 80%) that EITHER the true mean change in  $\text{PaO}_2/\text{FiO}_2$  OR mean change in Ventilation Index at 24 hours after last administration of surfactant “high” (e.g.,  $\geq 20\%$ ), either for an individual cohort or for all treated patients combined.

The following table shows the probability of observing at least 80% posterior probability that the true improvement is  $\geq 20\%$  on average for each endpoint.

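### The power table assumes 12 controls but the design randomises 8, so the stated dose-response power is about 2 to 10 points too high

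*Protocol*

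**What the plan says.** The power table in Protocol section 10 (Efficacy) is explicitly conditioned on the size of the control group: "The table below shows the power to show a significant dose response under varying assumed true dose response curves when using 12 matched controls". It covers five non-null response patterns at residual CVs of 20% and 25%. The text below the table draws a favourable conclusion for the smaller CV: "reasonable power to detect a dose response for either endpoint when the true increase is at least 20-30". The figure is a percentage, and the sentence requires such an increase in at least two of the cohorts.

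The design is fixed elsewhere in the protocol:

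- Section 4, treated patients: "3 patients will receive 10 vials (1080 mg) each of Alveofact" at each dosing time in cohort 1. The other three cohorts also have three treated patients each.
- Section 4, control arm: every cohort has "2 patients acting as controls (5 patients per cohort; total control n=8").
- Section 7.3: "Patients will be randomised to 3:2 for the treatment and control arms using ALEA Randomisation".
- Trial Summary, planned sample size: "Up to 20 hospitalised adult patients".

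**The concern.** The power figures describe a trial with four more controls than this one will have. All dose levels are compared with the control group, which is the largest single group, so cutting it from 12 to 8 lowers power in every pattern.

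These are the only operating characteristics the protocol gives for the dose-response test. If that test is not significant, readers will weigh the result against power that the design does not have. Section 10 also intends significant dose-response fits to help plan later studies, so readers need to know how likely such a fit is.

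**Working it through.** **Step 1. Count the controls.** Treated: 4 cohorts × 3 = 12. Controls: 4 cohorts × 2 = 8. Total: 20, which agrees with the 3:2 ratio and the planned sample size. With 12 controls the total would be 24. The protocol mentions no historical or external control set.

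**Step 2. Inputs for the simulation.**

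- From section 10: total doses of 0, 30, 50, 70 and 90 vials; a model-based multiple contrast test with linear and Emax candidates; residual CV of 20% or 25%; log transformation named as an option; power of 0.05 in the null rows.
- From section 4: 3 treated patients per cohort.
- Assumed, because the protocol does not give them: a one-sided 5% test and the Emax ED50 (20 vials in the table below, with other values tried).
- Model: group means ln(1 + change) and SD = √ln(1 + CV²), which is 0.198 at CV 20% and 0.246 at CV 25%. The test statistic is the larger of the two optimal-contrast t-statistics with pooled SD, referred to its simulated 95% point. Group sizes are n0/3/3/3/3.

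**Step 3. Reproduce the printed table with n0 = 12, then repeat with n0 = 8** (ED50 20; 100,000 runs per row).

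| CV | True change in cohorts 1/2/3/4 | Printed | n0 = 12 | n0 = 8 | Printed minus n0 = 8 |
|---|---|---|---|---|---|
| 20% | 10/20/30/40% | 0.89 | 0.904 | 0.850 | 0.040 |
| 20% | 25/25/25/25% | 0.82 | 0.815 | 0.719 | 0.101 |
| 20% | 0/25/25/25% | 0.75 | 0.745 | 0.676 | 0.074 |
| 20% | 0/0/30/30% | 0.72 | 0.711 | 0.663 | 0.057 |
| 20% | 0/0/0/50% | 0.63 | 0.648 | 0.617 | 0.013 |
| 25% | 10/20/30/40% | 0.77 | 0.765 | 0.689 | 0.081 |
| 25% | 25/25/25/25% | 0.66 | 0.652 | 0.553 | 0.107 |
| 25% | 0/25/25/25% | 0.57 | 0.582 | 0.513 | 0.057 |
| 25% | 0/0/30/30% | 0.54 | 0.548 | 0.499 | 0.041 |
| 25% | 0/0/0/50% | 0.49 | 0.486 | 0.458 | 0.032 |

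The null rows give 0.05 in both cases. With 12 controls every row agrees with the printed figure within 2 points for ED50 from 15 to 22.5 vials; ED50 of 5 or 10 misses by at most 2.2 points. The printed numbers therefore rest on 12 controls, and changing the word 12 to 8 without recomputing would leave wrong figures in place.

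**Step 4. Size of the loss.** Like for like (n0 = 12 against n0 = 8, same settings), power falls by 2 to 3 points when only cohort 4 responds and by 9 to 10 points in the flat 25% row. Against the printed figures the largest gap is 11.0 points, in the flat 25% row at CV 25% with ED50 22.5.

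**Step 5. Check by hand.** Compare all 12 treated patients with the controls for a flat 25% effect, one-sided 5%, using the normal approximation: power = Φ(ln 1.25 / [SD × √(1/12 + 1/n0)] − 1.645).

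- CV 20%: n0 = 12 gives Φ(2.760 − 1.645) = 0.87; n0 = 8 gives Φ(2.469 − 1.645) = 0.80.
- CV 25%: n0 = 12 gives Φ(2.220 − 1.645) = 0.72; n0 = 8 gives Φ(1.986 − 1.645) = 0.63.

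This cruder comparison loses 7 to 9 points, the same order as the simulation.

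**The case against.** The table is correct for the input it declares, so it contains no calculation error; the fault is a planning input that does not match the design. The trial is a pilot, and nothing says that the 20 patients were derived from this table. Section 4 rules out stopping for lack of efficacy. The interim rule that may prompt a larger trial is defined on changes in treated patients and tabulated after 6, 9 and 12 completers, so the number of controls does not affect it. Doses may also be repeated or reduced, which makes any power for a fixed 30/50/70/90-vial ladder nominal. All of this stands. It limits the consequences, but it does not make the printed figures apply to this trial.

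Three stronger readings are tempting, and the protocol does not support them.

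- A reader might infer a loss of 12 points or more. That size appears only under settings that fit the printed table worse, such as an ED50 of 45 vials, or that do not reproduce it, such as a two-sided 5% test on the log scale.
- A reader might treat the unstated sidedness as a fault in itself. Section 11.2 refers to a statistical analysis plan, where sidedness is commonly fixed.
- A reader might conclude that the sentence on reasonable power is reversed. It is not. The protocol treats 0.72 as reasonable and 0.63 as limited. At CV 20% with 8 controls, the four patterns with an effect in two or more cohorts give about 0.85, 0.72, 0.68 and 0.66: two are still at or above 0.72, and two fall between those levels.

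**Conclusion.** The inconsistency is certain and can be checked by counting: the power table uses 12 controls and the design provides 8. The stated power is too high by about 2 to 10 points, and by at most about 11 against the printed figures. The flat 25% row is affected most (0.82 to about 0.72 at CV 20%; 0.66 to about 0.55 at CV 25%), and the pattern with an effect only in cohort 4 is affected least.

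The direction does not depend on the assumptions. The sizes do: they rest on log-scale data, a one-sided 5% test and an Emax ED50 of about 10 to 22 vials, chosen because they reproduce the printed table with 12 controls. They also assume complete data, and section 10 analyses completers, so missing outcomes would lower power further.

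The practical effect is on how the dose-response result is read. Allocation, the interim rule and the stopping criteria are unaffected.

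**What to change.** Re-run the simulation with 8 randomised controls (2 per cohort) and replace the table and its lead-in sentence. Alternatively, if 12 controls are really intended, state where they come from and reconcile section 4, section 7.3 and the planned sample size with that.

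If the design stays at 8 controls, soften the conclusion under the table. At CV 20%, power is roughly 0.65 to 0.72 for a 25–30% effect in two or more cohorts, and about 0.85 only for the linear 10–40% pattern. The sponsor's own re-run should supply the final figures, because it will use the ED50 and test settings that the protocol does not state.

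The cost is one re-run of an existing simulation and a change of wording. Enrolment does not change. The only downside is that the stated figures become less favourable.
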